### Sample size calculation

Based on the postoperative length of stay found by Da Silva et al. [33], with a mean of 8.34 days (SD ± 10.32) and targeting a mean length of stay of 5.56 days (SD ± 10.32) after intervention, the sample calculation of REPLICCAR III was made using a two-tailed t-test for differences between two independent means. With a significance level of 5%, test power of 80%, and effect size of 0.27, the required sample size was determined to be 436 patients. Accounting for a 10% potential loss to follow-up, a final target sample size is 480 patients (240 per group). Sample size calculation was performed using G*Power software, version 3.1.9.4.

Because REPLICCAR III uses a stepped-wedge cluster randomized design, we incorporate the intra-cluster correlation (ICC), cluster size variability, and period effects (1 period = 2 months, time).

Design and allocation

We plan a cross-sectional stepped-wedge cluster randomized design 5 clusters (hospitals, K), 6 periods that includes the control phase (T), and an average of 16 patients per cluster-period (m), totaling K × T × m = 5 × 6 × 16 = 480 patients. All models will include fixed period effects to adjust for secular trends across time.

Correlation and cluster size variability.

Based on pilot information and published data on postoperative length-of-stay within hospitals, we assume a very low ICC = 0.001 and balanced recruitment across clusters (coefficient of variation of cluster sizes CV ≈ 0, achieved through monitoring and capped enrollment).

$$DE=\left[1+\left(m-1\right)\times ICC\right]\times \left(1+CV^{2}\right)$$

Under these assumptions, the standard design effect is:

DE≈1+15×0.001×=1.015(withCV≈0)

Therefore, with ICC = 0.001, CV ≈ 0, K = 5, T = 6, and m = 16, we will recruit N = 480 patients.

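### On the plan's own inputs, the first and last periods hold a third of the patients but almost no information on a constant effect, and stepped-wedge power is about 56%, not 80%

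*Protocol article*

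**What the plan says.** All of the sizing is in the protocol article, Methods, Sample size calculation.

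- The number of patients comes from a "two-tailed t-test for differences between two independent means", with control stay "with a mean of 8.34 days (SD ± 10.32") and "targeting a mean length of stay of 5.56 days (SD ± 10.32) after intervention". The settings are "With a significance level of 5%, test power of 80%, and effect size of 0.27". This gives 436 patients; after a 10% allowance for loss, "a final target sample size is 480 patients (240 per group").
- The layout is 5 hospitals, 6 two-month periods and "an average of 16 patients per cluster-period (m"), so 5 × 6 × 16 = 480.
- On the model: "All models will include fixed period effects to adjust for secular trends across time".
- The ICC is taken as 0.001 and hospital sizes as balanced ("CV ≈ 0, achieved through monitoring and capped enrollment"). The resulting design effect of 1.015 leaves 480 unchanged.

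The Randomization design section says that hospitals cross over in a staggered way and that data from the training phase are not analysed. The text does not give the step grid, a quota for each period, or power under the stepped-wedge model.

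**The concern.** With fixed period effects, the treatment effect is estimated mainly from comparisons between hospitals within the same period. A period in which all hospitals share one condition has no such comparison. It helps only by pinning down hospital effects, and an ICC of 0.001 says that there is almost nothing to pin down. If period 1 is all control and period 6 all intervention, a uniform 16 per cell puts a third of the patients where the planned model can use them least. It also means that the t-test's 80% does not describe the planned analysis. At stake are the trial's stated power and some precision that the timing of recruitment could recover at the same total.

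**Working it through.** **Inputs from the Sample size calculation section.** SD 10.32 (variance 106.5), difference 8.34 − 5.56 = 2.78 days, two-sided 5%, ICC 0.001, K = 5, T = 6, m = 16, fixed period effects.

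**Inferred layout.** One hospital crosses at each step: period 1 has no hospital on intervention, period 6 has all five. This gives 15 control and 15 intervention cells, and 15 × 16 = 240 per condition, which matches the plan.

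**Step 1: the plan's own figure.** d = 2.78 / 10.32 = 0.269. The noncentral t gives 218 per group, or 436, at 80.1% power. 436 × 1.10 = 480. The plan's figure reproduces.

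**Step 2: hand check at ICC 0.** With fixed period effects, the information is Σ m_t × k(5 − k)/5 divided by 106.5, where k is the number of hospitals on intervention in period t and m_t the patients per hospital in that period.

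- k(5 − k)/5 for periods 1 to 6 is 0, 0.8, 1.2, 1.2, 0.8, 0, which sums to 4.0.
- Uniform 16: 16 × 4.0 = 64, so SE = √(106.5/64) = 1.290 days.
- The unadjusted two-group comparison would have 240 × 240/480 = 120 in place of 64. That gap is why the t-test figure is too high.
- Periods 1 and 6 contribute exactly zero here.

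**Step 3: the plan's ICC.** Generalised least squares variance for a random hospital effect plus fixed period effects, total SD 10.32, power = Φ(2.78/SE − 1.96). At ICC 0.001:

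| Patients per hospital, periods 1–6 | N | SE (days) | Power |
|---|---|---|---|
| 16/16/16/16/16/16 | 480 | 1.314 | 56.2% |
| periods 1 and 6 deleted | 320 | 1.314 | 56.2% |
| 12/18/18/18/18/12 | 480 | 1.241 | 61.0% |
| 8/20/20/20/20/8 | 480 | 1.181 | 65.4% |
| 16/16/16/20/20/8 | 480 | 1.241 | 61.0% |

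For the uniform plan, 2.78/1.314 = 2.116, and Φ(2.116 − 1.96) = 56.2%. The end periods hold 2 × 5 × 16 = 160 of 480 patients (33%) and 0.11% of the information.

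**Step 4: dependence on the ICC** (values above 0.001 are assumptions).

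| ICC | Information in periods 1 and 6 | Power, uniform | 12/18×4/12 | 8/20×4/8 |
|---|---|---|---|---|
| 0.001 | 0.1% | 56.2% | 61.0% | 65.4% |
| 0.01 | 5% | 48.8% | 52.2% | 55.1% |
| 0.05 | 21% | 43.1% | 44.8% | 46.0% |
| 0.10 | 27% | 43.1% | 44.5% | 45.2% |
| 0.20 | 31% | 46.3% | 47.4% | 47.8% |

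**Step 5: other assumptions, uniform against 8/20×4/8.**

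- Hospitals as fixed effects: 37.7% against 38.5%.
- Cluster autocorrelation 0.8 at ICC 0.10: 34.5% against 35.7%.
- Half of each hospital's first intervention period lost to training, ICC 0.001: 48.9% against 57.6%.
- t reference with 4 degrees of freedom, ICC 0.001: about 37% against 44%.
- Separate effects for each of five exposure times, averaged equally, ICC 0.001: SE 1.556 against 1.562, so no gain. The SE for the longest exposure rises from 3.26 to 4.32 days, because period 6 is its only source.
- End quotas cut to 8 with the middle left at 16 (N = 400), ICC 0.05: power falls from 43.1% to 40.0%.

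**The case against.** Equal cells are the ordinary stepped-wedge layout, and the article contradicts nothing by using them. It speaks of an average, and its cap is described for balance between hospitals; no per-period cap is stated. The step grid is inferred, since the timeline figure is not shown. All of this stands, so the point is conditional on that grid and is not an error in the text.

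A reader might infer that the end-period patients are wasted and that those periods should be emptied. The documents do not support that. The 0.1% rests on an ICC of 0.001; at 0.05 and above the share is about 20% or more. Period 6 is also the only source for the longest exposure, and adherence during the intervention period is a secondary outcome. Training, an app and periodic meetings make an effect that grows with exposure plausible, and then the shift gains nothing.

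A reader might also infer that lower end quotas cost nothing if a hospital cannot exceed 16. That is wrong: if the middle does not fill, N falls to 400 and power drops at ICC 0.05.

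Feasibility is a fair challenge. The article gives no hospital volumes. If the excluded training month falls inside a two-month period, 20 patients in a crossing hospital means about 20 in one month. Recruitment began on 10 March 2025 for an expected year, so early periods may be closed. If only periods 5 and 6 can change (16/16/16/16/20/12), power is 58.2% at ICC 0.001 and 43.8% against 43.1% at 0.05.

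What survives the objection is the power figure. On the plan's own inputs and model, 80% is not reached.

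**Conclusion.** The point holds in a limited form, as something to consider. With one crossing per step, a constant effect, ICC 0.001 and a normal reference, the planned stepped-wedge model has about 56% power. The 160 patients in periods 1 and 6 then carry about 0.1% of the information on the effect. Moving some recruitment to the middle periods at N = 480 gains about 5 to 9 points at that ICC for the three patterns in the first table, and about 1 to 3 points at ICC 0.05 to 0.10. The gain is under 1 point with fixed hospital effects.

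Reallocation does not restore 80%. Sizing by an individual-level t-test that ignores the period adjustment is the larger problem, and the choice of cell sizes only moderates it. A small-sample reference for five hospitals lowers all these powers and, in the cases computed, keeps their order.

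**What to change.** 1. Restate the power from the stepped-wedge model with fixed period effects and the planned cell sizes, over a range of ICCs (for example 0.001 to 0.10), and state the step grid. This costs one recalculation.
2. Keep each hospital's total at 96 (N = 480). Let the remaining middle periods exceed 16 where volume allows, for example up to 18 to 20. Reduce a hospital's last-period quota only by the number it has actually recruited above 16, so that the total cannot fall. If periods 4 to 6 are still open, 16/16/16/20/20/8 is one such pattern.
3. State the downsides with the change: it needs spare hospital volume in the middle periods, and more where a training month is excluded; it leaves less information on long exposure; and it gives no gain if the effect varies with exposure time.

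The change adds no patients and no trial time. If the middle periods have no spare volume, only item 1 applies.

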## Introduction

Advances in cardiac surgery, driven by large databases, risk scoring systems, and technical innovations, have been significant [1–3]. However, the length of postoperative hospital stay remains a persistent challenge, especially within the Brazilian Unified Health System, where the average stay for coronary artery bypass graft (CABG) surgeries is approximately 11.8 days [4]. This issue is exacerbated by the lack of patient-centered protocols and misalignment within care teams [5–7].

Protocols based on the Enhanced Recovery After Cardiac Surgery (ERACS) concept aim to optimize care processes through a multidisciplinary, evidence-based approach, seeking to reduce both metabolic and psychological stress while fostering patient engagement in the recovery process [1,5,8]. Although promising, its implementation faces challenges related to management and adherence [9,10].

Digital platforms have shown potential to optimize outcomes by enhancing communication among healthcare teams and allowing better monitoring of care processes, thereby supporting adherence to protocol metrics [11–14]. These platforms have also demonstrated positive impacts on the patient and family education [15–17]. Within the context of rapid recovery, Schlund et al. [18] published a study on the use of a mobile application for patients undergoing elective colorectal surgery under the Enhanced Recovery After Surgery (ERAS) program, observing greater adherence to medication and shorter hospital stay, consistent with findings from other studies [19,20]. With the increasing use of mobile devices, health applications emerge as a promising means of promoting and facilitating health education.

In this context, the *Registro Paulista de Cirurgia Cardiovascular* III (REPLICCAR III) study seeks to analyze the impact of integrating a process customized application within enhanced recovery care pathways based on the concept of optimized recovery on postoperative hospitalization for patients undergoing CABG in the state of São Paulo, through the stepped-wedge cluster randomized design.

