### Statistical analysis

Variables will be compared using the chi-square test, Student’s t-test, or Kruskal-Wallis test. Categorical variables will be presented as numbers and percentages, while continuous variables will be presented as mean ± standard deviation (SD) or median and interquartile range (IQR). All analyses will be conducted using R software version 3.1.2 [32], within an integrated development environment for statistical computing and graphics, available in precompiled binary versions for Windows. Given the stepped-wedge cluster randomized design and the potential intra-cluster correlation, mixed effect models will be applied to evaluate possible cluster and period effects.

The randomization sequence for the five clusters (participating hospitals) will be computer-generated. Allocation will be hidden at both the cluster and patient levels, with prior knowledge limited to the project leader and the team responsible for sequence generation. Blinding will be maintained for the analysis of results.

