## Discussion

CABG is a primary therapeutic approach for treating coronary artery disease and one of the most performed and studied cardiac surgeries worldwide [34]. Despite ongoing technical and scientific advancements aimed at improving outcomes [2,35,36], prolonged hospital stay after surgery remains a significant challenge for healthcare teams who seek continuous improvement in patient care. In Brazil, the average length of stay after CABG in 2021 was 11,8 days [37], incurring an estimated cost of approximately 1 billion reais [38].

Factors such as inadequate preoperative preparation, disconnected care protocols, and decision-making based on outdated concepts are related to prolonged hospital stay, negatively affecting the patient experience and increasing the risk of complications, ultimately impacting prognosis [6,39–41]. Studies indicate that extended hospitalization is associated with higher rates of postoperative morbidity and mortality, in addition to imposing a financial burden on healthcare institutions [6,7,42–44].

Despite the proven benefits of optimized recovery pathways, their implementation in cardiac surgery is still rare and inconsistent, due to barriers related to interdisciplinary team interaction and communication [45–47]. In Brazil, a pioneering group developed first series of cases based on the Enhanced Recovery After Surgery concept, in the STS EACTS LATAM conference in 2019 [48], the same year that ERAS published its first guideline for cardiac surgery (ERACS) [24]. A subsequent detailed analysis of this series reported a median postoperative length of stay of 3 days while maintaining quality and safety standards and reducing negative outcomes [1]. However, the study also highlighted challenges related to adherence to metrics and effective communication among healthcare teams.

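### Power rests on one unsupported, time-constant ICC of 0.001 and a parallel-group calculation; under the planned stepped wedge 480 patients give about 56% power, and less if the ICC is larger or correlation decays

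*Protocol article*

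**What the plan says.** All of the sizing stands in the protocol article under Sample size calculation. It starts from a "two-tailed t-test for differences between two independent means", "with a mean of 8.34 days (SD ± 10.32) and targeting a mean length of stay of 5.56 days (SD ± 10.32) after intervention". The settings are given as "With a significance level of 5%, test power of 80%, and effect size of 0.27". The result is 436 patients, raised to 480 (240 per group) for 10% loss.

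The section then turns to the stepped wedge: five hospitals, six two-month periods, an average of 16 patients per hospital and period, and fixed period effects in all models. On clustering it says "we assume a very low ICC = 0.001 and balanced recruitment across clusters". The basis is described only as pilot information and published data; no estimate, interval, reference or range follows. A design effect with a single ICC and m = 16 gives 1.015, and 480 is kept.

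Under Statistical analysis, the article says that "mixed effect models will be applied to evaluate possible cluster and period effects". It does not name the random terms. The Introduction attributes long stay partly to a "lack of patient-centered protocols and misalignment within care teams", and the Discussion adds disconnected care protocols and calls the uptake of enhanced-recovery pathways in cardiac surgery rare and inconsistent.

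**The concern.** Two inputs carry the claim that 480 patients give 80% power: a two-group t-test, and an ICC so small that clustering appears to cost 1.5%. Neither describes this design. In a stepped wedge the intervention is partly confounded with calendar time, so adjusting for period takes away information that the t-test counts. The design effect used is the one for parallel clusters. It has no term for that adjustment, and none for correlation that weakens between periods.

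The ICC also looks very small for this setting. The trial expects a change in hospital processes to shorten the mean stay by 2.78 days, yet it assumes that hospitals with their own standard care differ with an SD of about a third of a day. That may be true, but no figure is shown.

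Two things are at stake. The trial may have much less power than stated, so that a real reduction in stay is missed. And if hospitals change over time each in their own way (staffing, beds, backlog) while the fitted model has only a constant hospital effect, the interval would be too narrow.

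**Working it through.** **Inputs from the Sample size calculation section.** Means 8.34 and 5.56 days (difference 2.78), SD 10.32, two-sided 5%, 80% power, K = 5, T = 6, m = 16, ICC 0.001, CV about 0, fixed periods. **Assumptions.** One hospital crosses over per period, so 15 of 30 cells are treated (15 × 16 = 240, which matches the stated 240 per group). ICCs other than 0.001, and every cluster autocorrelation (CAC, the correlation of a hospital's effect across periods), are assumed values.

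**1. The plan's own figures reproduce.** d = 2.78/10.32 = 0.269. The two-sample t-test needs 218 per group, or 436. 436 × 1.10 = 479.6, so 480. DE = 1 + 15 × 0.001 = 1.015. The design effect is never applied to N: 480 is the loss allowance alone, whereas 436 × 1.015/0.9 = 492.

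**2. What ICC 0.001 means in days.** Between-hospital SD = 10.32 × √ICC = 10.32 × 0.0316 = 0.33 days. So 95% of hospitals lie within 1.96 × 0.33 = 0.65 days of the overall mean. At ICC 0.01, 0.05 and 0.10 the SD is 1.03, 2.31 and 3.26 days.

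**3. The cost of adjusting for period, by hand, at ICC 0.** Without periods, the information on the treatment effect is 16 × 30 × 0.5 × 0.5 = 120, so SE = 10.32/√120 = 0.94. With fixed periods, only comparisons within a period count. With 0, 1, 2, 3, 4 and 5 of 5 hospitals treated, the sum of 5p(1 − p) is 0 + 0.8 + 1.2 + 1.2 + 0.8 + 0 = 4.0. The information is 16 × 4.0 = 64, and SE = 10.32/√64 = 1.29. The variance rises by 120/64 = 1.875. Power = Φ(2.78/1.29 − 1.96) = Φ(0.195) = 58%.

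**4. Adding the ICC.** The variance of the generalised least squares treatment estimate, with fixed periods, a random hospital effect and, for CAC below 1, a hospital-by-period effect, gives:

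| ICC | SE, CAC 1 | Power, CAC 1 | SE, CAC 0.8 | Power, CAC 0.8 |
|---|---|---|---|---|
| 0 | 1.290 | 58% | 1.290 | 58% |
| 0.001 | 1.314 | 56% | 1.311 | 56% |
| 0.01 | 1.440 | 49% | 1.439 | 49% |
| 0.02 | 1.501 | 46% | 1.520 | 45% |
| 0.05 | 1.557 | 43% | 1.652 | 39% |
| 0.10 | 1.555 | 43% | 1.780 | 35% |

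For example, at ICC 0.001: 2.78/1.314 − 1.96 = 0.156, and Φ(0.156) = 56%. Relative to ICC 0.001, the variance is 20% larger at ICC 0.01 ((1.440/1.314)²), 40% larger at 0.05, and 58% larger at 0.05 with CAC 0.8. If 10% are lost (m = 14.4), power is 52% at ICC 0.001 and 40% at 0.05 (CAC 1).

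**5. If only a hospital intercept were fitted while hospital-by-period variation exists.** The ratio r of true to model-based SE gives a type I error of 2(1 − Φ(1.96/r)):
- ICC 0.05, CAC 0.8: r = 1.07, 6.6%
- ICC 0.05, CAC 0.5: r = 1.16, 9.0%
- ICC 0.10, CAC 0.5: r = 1.31, 13.5%

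These take the variances as known. In simulated REML fits of the intercept-only model (2,000 runs, threshold 1.96) the error was 6 to 7% with no drift at all, 10 to 11% at CAC 0.8 and 11 to 15% at CAC 0.5 (ICC 0.05 and 0.10). In a smaller simulation (600 runs per setting) that fitted the hospital-by-period term, the error stayed near 9% at CAC 0.5. The extra term alone is therefore not enough with five clusters.

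**The case against.** The strongest reply is that nothing shows the ICC to be wrong. A reader might infer that 0.001 contradicts the plan's own premise. It does not. The Introduction and Discussion describe a system-wide problem and give no variation among the five hospitals. If all five are similarly slow, a large common effect and a small ICC can coexist. The article also says that it rests on pilot and published data, which are not shown. This stands: the ICC is unsupported and in tension with the premise, no more.

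Nor do the two averages help. The Discussion says "the average length of stay after CABG in 2021 was 11,8 days", against 8.34 postoperative days in the sizing. These are aggregates from different sources, perhaps with different definitions, and do not measure differences between these five hospitals. It would also be wrong to read 0.65 days as the distance between hospitals: it is the distance from the overall mean. Two hospitals can differ by about 1.96 × √2 × 0.33 = 0.9 days.

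A reader might also blame the ICC for the whole power gap. Most of it is present at ICC 0. Nor does power keep falling as a constant ICC grows: it levels off at 43% for ICC 0.05 to 0.10 and is 46% at 0.20.

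Finally, one might say that the stated model gives too narrow an interval. The article does not state the random effects, does not exclude a hospital-by-period term, and may leave this to an analysis plan that is not shown. The interval point is conditional for that reason.

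**Conclusion.** The concern holds in this form. The stated 80% does not follow from the design as described: with the plan's own inputs, power at 480 patients is about 56%. The main cause is that the t-test and the parallel-cluster design effect leave out the period adjustment. The single, time-constant ICC of 0.001 makes the figure more fragile. Assumed ICCs of 0.01 to 0.10 take off a further 7 to 13 points, and with CAC 0.8 the loss reaches about 21 to 22 points (35% at ICC 0.10).

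If a hospital intercept alone were fitted and hospital-specific drift exists, the large-sample type I error would be about 7 to 14% over ICC 0.05 to 0.10 and CAC 0.5 to 0.8. Whether that model is planned cannot be told from the article.

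The results rest on one crossover per period, 16 analysed patients in every cell and normal-theory power. They are large-sample figures: with a t reference on 4 degrees of freedom, as one conservative choice, power at ICC 0.001 would be 37%. The article gives no data on the true ICC, so the lower powers are a range and not an estimate.

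**What to change.** 1. Replace the t-test and the 1.015 design effect by a stepped-wedge power calculation with fixed periods. Restate power at N = 480 over a range of ICC (for example 0.001 to 0.05) and autocorrelation (0.8 to 1), and give the source of the ICC. The group's REPLICCAR II database could inform both values if it holds hospital and date identifiers; the article does not say whether it does, or whether it covers these five hospitals.

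2. Specify the primary mixed model before analysis: fixed periods, a hospital random effect, a hospital-by-period random effect, and a small-sample correction suited to five clusters.

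The work is one analysis of existing registry data, if feasible, and one extra variance term. The price is a less favourable stated power, and an interval that is somewhat wider than necessary if hospitals do not drift. Recruitment was still under way when the article was written, so both changes could be made before the outcome is analysed.

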### Randomization design

Randomization of hospitals/reference centers (clusters) will be performed at the beginning of the project. Allocation will be carried out by an independent statistician and kept confidential by the study coordinating center. Hospitals will be informed of their assignment to the intervention group one month before the training of their multidisciplinary teams on the application incorporating the study protocols.

Each cluster will be randomly assigned to the intervention group in a staggered fashion:

**Control period:** While the hospital is not randomized to the intervention group, data will be collected from the “control” period, consisting of observational data from standard care practices.**Implementation and training period:** Data from this period will not be analyzed, as it serves as an adaptation phase. Training on the application and optimized recovery protocols will be carried out through classes, meetings, and training sessions (with support from the STRATUS Center for Medical Simulation, Brigham Health) to ensure correct system use and adherence to the care protocol, using the intervention of *Tempos Certos* Protocol [23], based on Enhanced Recovery After Cardiac Surgery (ERACS) [24] concepts adapted to the context of the Brazilian Unified Health System.**Intervention period:** After the implementation period, collected data will be assigned to each hospital’s “intervention” group. As the project progresses, periodic meetings will be held to address challenges and provide updates on care at each institution.

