### Database

The Cardux platform (https://cardux.net/, Fig 3) and REDCap [30] will be used for secure data storage, accessible by username and password for both study phases. Variables collected during the study will be based on insights from the REPLICCAR II project [31], addressing data related to patient demographics (e.g., gender, age, comorbidities), pre-, intra- and postoperative phases (e.g., clinical exam results, use of cardiopulmonary bypass, need for blood transfusion, complications), as well as hospitalization metrics (e.g., length of surgical procedure, postoperative intubation time, length of hospital stay). In addition, follow-up data will be collected at 30 days and 6 months post-discharge, including variables such as need for readmission, further interventions, incidence of acute myocardial infarction, mortality, and variables related to PREM and PROM analysis.

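### Recruiters know the hospital's phase and the article's model names only cluster and period, so a case-mix change at crossover would read as an effect on stay

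*Protocol article*

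**What the plan says.** **Recruitment.** A project representative at each hospital obtains consent (Methods, text after Fig 1), and every patient consents in writing whichever phase the hospital is in (Ethical approval and informed consent). Hospitals learn of their move to the intervention one month before training (Randomization design). In the intervention phase the site study group helps patients install the app while recruiting them (Intervention application). Blinding is stated only for the analysis of results (Statistical analysis).

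**Who can enter.** Elective and urgent primary isolated CABG are both eligible. Patients must be proficient with a phone, and disabilities that would prevent adherence exclude (Study population). The Discussion says familiarity with phones was required for the sake of adherence.

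**The cap.** The Sample size calculation takes the variation in cluster size as about zero, "achieved through monitoring and capped enrollment", with an average of 16 patients per cluster-period.

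**The model.** The Statistical analysis section applies mixed models for cluster and period effects, and the Sample size calculation puts fixed period effects in all models. No patient-level covariate is named. Patient data are collected, "addressing data related to patient demographics (e.g., gender, age, comorbidities" being the examples given in the Database section.

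**Who holds the sequence.** Randomization design: "Allocation will be carried out by an independent statistician and kept confidential by the study coordinating center". Statistical analysis: allocation is hidden, "with prior knowledge limited to the project leader and the team responsible for sequence generation".

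**The concern.** Randomising the order in which five hospitals cross over balances the hospitals' characteristics in expectation. It does not protect the step at which individual patients are approached and consented by staff who know whether the pathway and app are running. Some eligibility criteria call for judgement, and they may be applied differently once there is a pathway to adhere to and adherence is watched in real time. Urgency leaves further room for the mix to move. A cap means that a busier hospital may leave eligible patients out.

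If lower-risk patients are enrolled after crossover, their shorter stay is credited to the intervention. If higher-risk patients are enrolled, a true benefit is hidden. Postoperative stay is the primary outcome, so the main result is exposed.

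**Working it through.** **1. The plan's own figures.** The inputs are a control stay "with a mean of 8.34 days", a target of "5.56 days (SD ± 10.32) after intervention", and "With a significance level of 5%, test power of 80%, and effect size of 0.27".

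- Difference: 8.34 − 5.56 = 2.78 days; 2.78 / 10.32 = 0.269.
- An exact two-sided t-test gives 218 per group, 436 in all; 436 × 1.10 = 479.6, rounded to 480.

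Both 436 and 480 reproduce. They bear on sample size, not bias; only the 2.78-day target and the SD are carried forward.

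**2. Why cluster and period terms leave the bias in.** Write a patient's stay in hospital *i*, period *j* as

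Y = period_j + cluster_i + θ·X_ij + γ·Z + error,

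where X_ij is 1 after crossover, Z marks a long-stay patient (for example urgent), and γ is the difference in mean stay. Let the share with Z = 1 be a_i + b_j + δ·X_ij. Leaving Z out gives

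E[Y] = (period_j + γ·b_j) + (cluster_i + γ·a_i) + (θ + γ·δ)·X_ij.

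Lasting differences between hospitals go into the cluster term and secular changes in case mix into the period term. The part that starts at each hospital's own crossover stays with the treatment term: **bias = γ × δ**.

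**3. Standard error.** Assumptions: one hospital crosses per period, no cells are excluded, and K = 5, T = 6, m = 16 and ICC = 0.001 as in the article.

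- Total variance 10.32² = 106.50; between-hospital τ² = 0.001 × 106.50 = 0.1065; cell-mean variance s² = 0.999 × 106.50 / 16 = 6.650.
- U = 5+4+3+2+1 = 15; W = 0+1+4+9+16+25 = 55; V = 25+16+9+4+1 = 55.
- Var = K·s²·(s² + Tτ²) / [(KU − W)s² + (U² + KTU − TW − KV)τ²] = 5 × 6.650 × 7.289 / [20 × 6.650 + 70 × 0.1065] = 242.3 / 140.4 = 1.726.
- **SE = 1.31 days.** The two-sample SE is 10.32 × √(2/240) = 0.94 days.

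**4. Size of the bias.** The documents give neither γ nor δ, so both columns of inputs are assumed. False-positive rate = Φ(b/SE − 1.96) + Φ(−b/SE − 1.96).

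| Gap γ (days) | Shift δ (points) | Bias b (days) | Share of 2.78 | Rate, SE 1.31 | Rate, SE 0.94 |
|---|---|---|---|---|---|
| 3 | 5 | 0.15 | 5% | 5.1% | 5.3% |
| 3 | 10 | 0.30 | 11% | 5.6% | 6.2% |
| 5 | 10 | 0.50 | 18% | 6.7% | 8.3% |
| 5 | 20 | 1.00 | 36% | 11.9% | 18.6% |
| 5 | 30 | 1.50 | 54% | 20.8% | 35.7% |
| 10 | 30 | 3.00 | 108% | 62.7% | 89.0% |

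Signs are omitted, because the shift can go either way.

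**5. Precision gained by adjustment.** If baseline covariates explain a share R² of the variance (assumed), power = Φ(2.78 / (1.3136·√(1 − R²)) − 1.96).

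- R² = 0: Φ(0.156) = 56%.
- R² = 0.10: Φ(0.271) = 61%.
- R² = 0.20: Φ(0.406) = 66%.

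These are on the high side, because implementation-period data are not analysed. If the one-month training removes half of each hospital's first two-month intervention cell, SE is 1.44 and power without covariates is 49%.

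**The case against.** Several stronger readings are tempting, and the documents do not support them.

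- **No risk adjustment is planned.** This would rest on silence. The article names no patient covariate but excludes none, and a covariate list is commonly left to the SAP, which is not shown. A consecutive-enrolment rule and a screening log may likewise stand in the full protocol.
- **The project leader steers recruitment.** The leader knows the order in advance, but consent lies with site representatives and app introduction with the site study group. The two statements on who holds the sequence can be read together: a statistician allocates, the coordinating side holds the list, and hospitals hear one month before training.
- **Staff choose who fills sixteen places in each phase.** The cap is stated as a means to balance across hospitals, and 16 is an average. No cap per cell or phase is given.
- **The bias is large.** At the 10-point, 3-day example the false-positive rate moves only from 5.0% to 5.6%. The article also narrows the case mix to primary isolated CABG with glycosylated haemoglobin of at most 8%.

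All of this stands. What remains is that recruiters know the phase. Statements that allocation is hidden at patient level can hold only before crossover, and the model as described would not separate a case-mix change at crossover from a treatment effect.

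**Conclusion.** The concern holds in limited form. Individual recruitment by staff aware of the phase, mixed urgency among eligible patients, and a model described only by cluster and period leave the primary estimate open to a case-mix change at crossover. The direction is not known and the size cannot be fixed from the documents: 0.3 days in the modest example, and 0.15 to 3.0 days over assumed gaps of 3 to 10 days and shifts of 5 to 30 points. Nothing in the article shows that such a shift has occurred. The case for naming covariates does not depend on one: with power near 56% under the article's own ICC and the assumed rollout, the precision gain is useful in itself.

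**What to change.** **Model.** Prespecify in the primary mixed model, beside cluster, period and treatment, a short set of preoperative covariates: age, sex, elective or urgent status, and comorbidities including diabetes and renal function. Use nothing measured after surgery starts. Values at enrolment are preferable, because the app supports prehabilitation before surgery. The Database section names age, gender and comorbidities. Urgency, glycosylated haemoglobin and creatinine clearance appear in the eligibility criteria and so should be known at screening; confirm that each is a recorded field. If the SAP already lists covariates, check it against this set.

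**Enrolment.** For the remaining periods, fill capped places with consecutive eligible patients, and report screened, eligible and enrolled counts by phase, with baseline characteristics by phase.

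**Cost and limits.** The model change is wording, made before the analysis, and a few degrees of freedom. The log is one sheet per site. Adjustment deals with measured factors only. Recruitment had begun by the time of the article, so the enrolment rule cannot reach patients already entered; for them, screening counts can be given only where records exist.
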